#### Change from baseline in other relevant laboratory parameters

Change from baseline during treatment until Day 15 with measurements performed days 1, 4, 7 and 15 or until hospital discharge of the following parameters will be summarized using descriptive statistics:

- WBC with differential counts
- RBC
- Hb

- 
- Platelet count
  - Fibrinogen
  - Prothrombin Time
  - Cardiac troponin
  - Liver tests (AST, ALT, total bilirubin levels)
  - Creatinine

#### 6.3.6 Interim analysis

The study will consist of one interim analysis (Stage 1 - treatment) and a final analysis (Stage 2 – follow-up), with approximately the same numbers of patients randomized into Stage 1 and into Stage 2 per treatment arm. The Stage 1 interim analysis will be conducted after the accrual of at least 25 patients per treatment arm.

#### 6.3.7 Multiple comparison/multiplicity

There will be no adjustments for multiplicity for the two pairwise treatment comparisons for the primary endpoint. Multiplicity for the sequential comparisons at the end of Stage 1 and at the end of Stage 2 are however accounted for by the design.

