## 6 Statistical plan

### 6.1 Determination of sample size

The study will enroll a total of 180 patients, 90 per arm according to the 1:1 randomization. The sample size has been estimated based on the following assumptions:

- The sample size is calculated in based of the data collected in the database of COVID-19 of the Complejo Hospitalario de Navarra , which currently has a total of 188 patients. After the analysis of the data, it is estimated that 15% of severe pneumonia COVID patients have required mechanical ventilation.
- For and Type I error of 0.05 and a power of 75% for each comparison under the assumption that the true success rates are 88% in the SoC group increasing to 92% in the anakinra group.
- It is needed 180 patients (90 per arm) considering a loss of 10%.
- The study will consist of two stages, with equal numbers of patients randomised into Stage 1 (treatment) and into Stage 2 (follow-up) per treatment arm.

The calculations on the operating characteristics of this design have been undertaken using the website of Sample size calculator of *National Center for Advancing Translational Sciences, National Institutes of Health*, through [UCSF-CTSI](#) , Software utilities developed by [[contact]](mailto:[contact]), last up to date version on April 14, 2020.

The value for the type I error has been chosen in recognition of the urgent unmet medical need to allow the identification of a signal, at least, from a statistical perspective. Having seen a statistical signal, it is then a matter of evaluating whether the observed treatment differences represent clinically relevant effects that can satisfy that unmet need.

In case indications of efficacy requires to be confirmed, additional patients may be added into this study.

In case the outcome is statistically convincing, efficacy will be considered confirmed and the results will, where warranted, be used to seek regulatory approvals.

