### 6.3.1 General statistical issues

This design has acceptable properties in terms of the false positive potential, controlling the overall type I error at 5%, for each of the two treatment comparisons.

Secondary endpoints will be evaluated in a descriptive way. In some cases, p-value comparisons will be undertaken, but these are to be interpreted in an exploratory way.

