### 6.3.3 Analysis related to primary objective

#### *6.3.3.1 Primary endpoint*

##### Treatment success

The main outcome variable is the percentage of patients requiring mechanical ventilation at 15 days after the start of treatment. The comparison of these proportions would be done by chi-square test, with significance level 0.05 and presentation in the form of absolute risk

reduction, relative risk reduction and number needed to treat, with their respective 95% confidence intervals.

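### The protocol claims 5% overall type I error for its two-stage design, but the design it describes contains nothing that secures this, and the option to add patients has no alpha rule

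*Protocol*

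**What the plan says.** - **Claim of control.** Section 6.3.1 describes the design as "controlling the overall type I error at 5%, for each of the two treatment comparisons". Section 6.3.7 adds "Multiplicity for the sequential comparisons at the end of Stage 1 and at the end of Stage 2 are however accounted for", attributing this to the design itself. The same section declines to adjust for two pairwise treatment comparisons.
- **Looks.** Section 6.3.6: "The study will consist of one interim analysis (Stage 1 - treatment) and a final analysis (Stage 2 – follow-up"). On the size of the two stages, the section has them proceed "with approximately the same numbers of patients randomized into Stage 1 and into Stage 2 per treatment arm". It then says "The Stage 1 interim analysis will be conducted after the accrual of at least 25 patients per treatment arm". It gives no boundary, spending function, stopping rule or nominal level.
- **Primary test.** Section 6.3.3.1: "The comparison of these proportions would be done by chi-square test, with significance level 0.05". Section 6.1 sizes the trial at a type I error of 0.05, with 90 per arm.
- **Extension.** Section 6.1: "In case indications of efficacy requires to be confirmed, additional patients may be added into this study". It gives no trigger, number or retest level. It also says that a statistically convincing result will count as confirmation of efficacy and may support regulatory applications.
- **Arms and blinding.** Sections 4.1 and 4.4.3 describe two arms, hence one treatment comparison. Section 4.4.6 says the study is open.

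**The concern.** Type I error control over two looks needs a mechanism: a boundary at the interim and, usually, a slightly lower level at the end. The protocol says the design supplies one, but the design as written has only the full 0.05.

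The stage definitions do not help. Treatment and follow-up are consecutive phases of the same patients, as section 4.1 describes them, while sections 6.1 and 6.3.6 speak of patients being randomised into each stage. Only the second reading gives a sequential design, and the protocol does not say which is meant.

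The extension clause is a separate gap. Adding patients because the data look promising and then retesting is a further look, and the statement in section 6.3.7 covers only the ends of Stages 1 and 2.

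At stake is the confirmatory claim in section 6.1. In an open study, an interim level, interim size or extension chosen after data have been seen would leave the 5% figure without support.

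**Working it through.** **Inputs.** Final size 90 per arm (section 6.1). Interim at 25 per arm, the minimum allowed, or 45 per arm, implied by equal stages (section 6.3.6). Level 0.05 (sections 6.1 and 6.3.3.1). Assumptions: the test is two-sided (the protocol does not say), and the stages are sequential cohorts.

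**The stated figure.** The 5% cannot be derived from the protocol, because no interim level is given. It can be reached only by supplying a rule. As a check of the method, the standard two-look boundaries at half information (2.178 at both looks, or 2.797 then 1.977) both return 5.0%.

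**Two looks at the only stated level.** Under the null hypothesis the two z-statistics have correlation √(n₁/n₂).

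Overall error = 1 − P(|Z₁| ≤ 1.96 and |Z₂| ≤ 1.96)

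- Interim at 25: correlation √(25/90) = 0.527, error 9.0%.
- Interim at 45: correlation √(45/90) = 0.707, error 8.3%.

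**Extension and retest at 0.05 after any miss** (r = enlarged size divided by 90 per arm):

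| r | No interim test | Interim at 45 | Interim at 25 |
|---|---|---|---|
| 1.25 | 7.1% | 10.1% | 10.9% |
| 1.5 | 7.7% | 10.7% | 11.4% |
| 2.0 | 8.3% | 11.3% | 12.0% |

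If the trial is extended (r = 1.5 or 2.0) only when the final p lies between 0.05 and 0.20, the error with an interim test is 9.8–10.7%.

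**Binomial simulation of the chi-square test** (success 85%, 88% or 90% in both arms; interim at 25 or 45; extension to 135 or 180 per arm):

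| Test | Two looks | Two looks plus extension |
|---|---|---|
| Uncorrected | 8.6–9.3% | 11.0–12.4% |
| Continuity-corrected | 2.9–4.5% | 4.8–6.8% |

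**Two looks with a strict interim boundary, final test left at 0.05:**

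- Interim p<0.001: 5.05% at 25 per arm, 5.02% at 45 per arm.
- O'Brien-Fleming-type interim boundary at half information: 5.2%.

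**Levels that restore exactly 5%:**

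- Interim p<0.001: final 0.0495 (25 per arm) or 0.0498 (45 per arm).
- O'Brien-Fleming-type spending at half information, α(t) = 2[1 − Φ(1.96/√t)]: 0.0056 at the interim, 0.0478 at the final.

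**The case against.** The strongest reply is that the protocol never sets the interim at 0.05. It says the looks are accounted for, and a boundary may stand in a statistical analysis plan that is not shown. This stands as far as the numbers go: a reader might infer that the true error is 8–12%, but the documents do not support that. With a strict boundary, even an unreduced final 0.05 costs at most about 0.2 percentage points. The reply does not rescue the claim itself. The protocol asserts control by a design that it describes, and no such rule is in it. A two-look boundary held elsewhere would also not cover the extension.

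Four further points:

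- **Continuity correction.** Section 6.3.3.1 says only "The comparison of these proportions would be done by chi-square test" and does not mention a correction. With one, two looks at 0.05 stay below 5%, though an extension can still take the error to 6.8%. This stands as a condition on the figures.
- **Stage labels.** If Stage 1 means Day 15 and Stage 2 means Day 28 in the same patients, the primary endpoint could be tested once, since ventilation at Day 28 is a secondary endpoint. The two-look figures would then not apply. The wording about randomising into each stage prevents settling this, so it must be clarified.
- **Interim timing.** One might read 25 per arm and equal stages as a contradiction. They are not: 25 is a floor, and 45 satisfies it. The timing is merely unfixed.
- **Sidedness.** The figures are two-sided; about half of each, roughly 4–6%, is a false claim of benefit.

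The mention of two treatment comparisons is stray wording that does not change the error.

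**Conclusion.** The point holds in this form: 5% control is claimed, but the design described does not deliver it, and the extension clause lies outside any control claimed. Testing each look at the only stated level, two-sided and uncorrected, in sequential cohorts gives about 8–9%. One unadjusted extension and retest raises this to about 10–12%; the 12% end needs an interim at 25 per arm, a doubled sample and a retest after every miss. Extension without an interim test gives about 7–8%. Under a strict boundary, or with a continuity correction, the two-look error is about 5.0–5.2% or 3–4.5% respectively. None of these is the trial's actual error rate, which the protocol leaves undetermined. Because section 6.1 ties a confirmatory claim to the result, this should be settled before any comparative look at the data.

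**What to change.** 1. **Interim.** Either state that it is non-inferential for efficacy, with no test and no efficacy claim, or fix one interim size with an explicit boundary and final level. Examples: p<0.001 at the interim with a final level of 0.0495 (25 per arm) or 0.0498 (45 per arm); or O'Brien-Fleming-type spending at half information, with 0.0056 and 0.0478. State sidedness and whether the chi-square is continuity-corrected.
2. **Primary test.** Carry the chosen final level into sections 6.1 and 6.3.3.1, so that 6.3.1 and 6.3.7 describe a rule that exists.
3. **Extension.** Replace the sentence in section 6.1 with a pre-specified combination test (trigger, maximum number added, weights), or say that any extension is a new trial.
4. **Wording.** Define the stages in sections 6.1 and 6.3.6 as either patient phases or sequential cohorts. Remove the references to two treatment comparisons in 6.3.1 and 6.3.7.

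The cost is protocol wording and a final level of about 0.048–0.050 in place of 0.05. A non-inferential interim with no extension keeps the full 0.05.

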#### 6.3.8 Handling of missing data

There will be no computation of missing data.

---

## 7 Data collection, handling and record keeping

### 7.1 Data standards

Collection of data should be performed in the CDASH format, according to the CDISC. The standards should be used to the extent possible and/or required for the specific study/project. The minimum requirement of the CDISC standard is to collect all core variables specified as 'Required' in the Study Data Tabulation Model format.

### 7.2 Case report form

A CRF is required and should be completed for each included patient. In this study, a paper CRF will be used to capture all study data except for the scheduled laboratory results from the hospital's local laboratory.

It is the responsibility of the Principal Investigator to ensure the completeness, legibility, and accuracy of the data reported in the CRF, to review and to confirm these by proving his/her signature, thus approving all CRFs pages. The Principal Investigator must sign off each visit in the CRF using black ballpoint pen, in addition to providing a final signature of the completed CRF. These signatures serve to attest that the information contained on these CRFs is correct. At all times, the investigator has final responsibility for the accuracy and authenticity of all clinical and laboratory data entered on the CRFs.

In either case, it is important that the original CRF pages remain at site.

### 7.3 Source data

Patient source documents are the patient's medical records maintained at the study site. In most cases, the source documents will be the hospital's or the physician's chart, including laboratory test results, radiology results, EKG etc. In those cases, the information collected in the CRFs must match those charts.

A separate source document location agreement will be completed and signed by the Principal Investigator and the site monitor.

Source data should be attributable, legible, contemporaneous, original, accurate, and complete. Changes to source data should be traceable, should not obscure the original entry, and should be explained if necessary (e.g. via an audit trail).

## 7.4 Protocol deviations

A protocol deviation is generally an unplanned excursion from the protocol that is not implemented or intended as a systematic change. The investigator is responsible for ensuring the study is conducted in accordance with the procedures and evaluations described in this protocol and must protect the rights, safety, and welfare of patients. The investigator should not implement any deviation from, or changes of, the protocol, unless it is necessary to eliminate an immediate hazard to study patients.

A protocol waiver is a documented prospective approval of a request from an investigator to deviate from the protocol. Protocol waivers are strictly prohibited.

The investigator will assure that deviations are reported and documented in accordance with IEC and applicable regulatory requirements.

## 7.5 Database closure

Prior to database closure, all tasks or criteria defined in the data management plan must be completed and documented. The study database must be locked before generation of any results. The database lock will be approved by relevant study personnel and all edit accesses will be removed. Following database closure, the study database can only be unlocked in case critical errors, affecting the main conclusions of the study, are discovered.

## 7.6 Record retention

The investigator should maintain a record of the location(s) of investigator's essential documents as defined in the ICH GCP Guideline [1] including source documents and should have control of and continuous access to all essential documents and records generated by the investigator/institution before, during, and after the study.

All documents and data relating to the study will be kept securely by the investigator in a secure file and/or electronically. The storage system used during the study and for archiving

(irrespective of the type of media used) should provide for document identification, version, history, search and retrieval. The data will be available for evaluation and/or audits from Health Authorities, Sponsor or Sponsor's representatives.

When a copy is used to replace an original document (e.g. source documents, CRF), the copy should fulfill the requirements for certified copy as defined in ICH GCP Guideline [1].

The records should be retained by the Investigator as specified in the Clinical Trial Agreement and in accordance with local regulations.

If the investigator relocates, retires, or for any reason withdraws from the study, the study records may be transferred to an acceptable designee, such as another investigator or another institution.

---

## 8 End of study

The end of this study is defined as the date of the last patient's last visit/end of study call.

---

## 9 Sponsor's discontinuation criteria

The Sponsor and GEAS through the Principal Coordinating Investigator, reserve the right to discontinue the study prior to inclusion of the intended number of patients but intends only to exercise this right for valid scientific or administrative reasons. After such a decision, the investigator must contact all participating patients within 30 days. All study materials must be collected and all the CRFs completed to the greatest extent possible.

---

## 10 Dissemination and publication of results

The study information and post study results regardless of outcome will be published on a publicly accessible website in accordance with applicable laws and regulations, e.g., on [www.clinicaltrials.gov](http://www.clinicaltrials.gov) and EudraCT. The results of this study will be published within 12 months of the end of study.

The Sponsor is committed to publishing study results in a complete, accurate, balanced, transparent and timely manner. The Sponsor follows the principles of the International Committee of Medical Journal Editors (ICMJE) recommendations for the conduct, reporting, editing, and publication of scholarly work in medical journals including criteria for authorship.

The data from this study will be considered for reporting at a scientific meeting or for publication in a scientific journal. The Sponsor will be responsible for these activities and will work with the investigators to determine how the publication is written, the number and order of authors, the journal or scientific meeting to which it will be submitted, and other related issues. The results of the study, or any part thereof, shall not be published without the prior written consent and approval of the Sponsor and GEAS through the Principal Coordinating Investigator, such consent and approval not to be unreasonably withheld.

